### Participants

Sixty comorbid alcohol dependent and depressed patients, 30 alcohol dependent only and 30 depressed only patients will be included for T1 assessment. Further, 30 healthy control participants (matched according to age, gender and educational level) will be recruited.

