### Sample size

Power calculations were conducted by means of the G*Power 3.1 software package [46]. According to pilot studies, an effect size of at least d = 1 can be assumed for the different paradigms and comparisons. For region of interest analysis with regions of 200 voxels, a sample of 30 per group should be sufficient to reach a power of 80% to detect differences at *p* < .05 (Bonferroni corrected for multiple tests). For the intervention study the same comorbid alcohol dependent and depressed participants will be randomly assigned to one of two group therapy interventions and asked to participate in a second fMRI session and follow up measurement. When assuming a small to medium effect size (*f* = .2) for the group x time interaction and a correlation among repeated measures of.7 (as typical for fMRI data), we achieve a power of 80% to detect differences at *p* < .05 (Boferroni corrected for a k = 200, region of interest) on the neural level even when we have to face a drop-out rate of 10%. While we expect an attrition rate of 20%, recruitment will be continued until the desired sample sizes are reached and drop-outs will be replaced by new participants.

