### Behavioral data analyses

Analysis will be completed by using (repeated measures) analysis of variance (AN(C)OVA) in order to test group differences (AUD vs MD vs Co vs HC) and treatment groups (BAT vs MBT). Difference scores will be calculated. All measures will be compared between groups, as well as treatment groups and interaction effects will be explored. Wherever appropriate, missing data will be imputed using multiple imputation.

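### BAT versus MBT is powered on the change from T1 to T2, with no commitment to the T1 value as covariate; ANCOVA on T1 would cut the variance by about 15% at the protocol's own correlation

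*Protocol article*

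**What the plan says.** **Sample size.** The intervention part is powered as follows: "When assuming a small to medium effect size (*f* = .2) for the group x time interaction", with "a correlation among repeated measures of.7 (as typical for fMRI data". The claim is that "we achieve a power of 80% to detect differences at *p* < .05 (Boferroni corrected for a k = 200, region of interest", allowing for 10% drop-out.

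**Behavioral data analyses.** The model is given as: "Analysis will be completed by using (repeated measures) analysis of variance (AN(C)OVA", for both the four diagnostic groups and the two treatment arms. The same paragraph says: "Difference scores will be calculated". Interaction effects are to be explored. No covariate is named, and the text does not say which analysis decides BAT versus MBT.

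**Table 1 (Predictors).** The fMRI battery is scheduled at T1 and T2. Craving, depression and most other scales are scheduled at T1, T2 and T3.

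**Randomization.** Comorbid patients are allocated after the baseline assessment is complete, so T1 values are pre-randomisation.

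**Activation and Connectivity fMRI analysis.** These sections describe first-level and connectivity methods. For the neural outcomes, the power statement is therefore the only indication of how the arms will be compared over time.

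**The concern.** With two time points, the group-by-time interaction of a repeated-measures ANOVA is identical to a two-sample t-test on difference scores. What the article states positively about the randomised contrast, namely the powered test and the planned difference scores, therefore points towards analysing change. The bracketed C in AN(C)OVA does not settle the matter. A covariate such as age, added to a model that keeps T1 as an outcome, does not adjust the change for T1; only the patient's own T1 value does.

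Change scores subtract the whole T1 value, although only a fraction r of it (at equal SDs) predicts T2. The remainder adds noise. Any chance difference between arms at T1 also carries into the change through regression to the mean. The comparison has 60 patients at most, and T1 is measured before allocation, so this loss is avoidable.

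**Working it through.** **Inputs**
- 60 comorbid patients (Participants), and 54 after the 10% drop-out in the power statement: 60 × 0.9 = 54.
- f = .2, r = .7, Bonferroni correction for k = 200 (Sample size).
- Assumed: equal SDs at T1 and T2, equal arms, independent patients.

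**The plan's own figure first.** For the two-group, two-time interaction, λ = f² × N × 2/(1 − r), with 1 and N − 2 degrees of freedom. At N = 54, λ = 0.04 × 54 × 2/0.3 = 14.4. Power is 96.1% at α = .05, and 45.6% at α = .05/200 = .00025 (reading k = 200 as 200 tests). At N = 60 the figures are 97.6% and 54.3%. The stated 80% is not reproduced on either reading; that is a separate matter.

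An f of .2 is a BAT–MBT difference in change of 4 × 0.2 = 0.8 SD. The same λ follows from the change-score variance: (54/4) × 0.64/0.60 = 14.4. This confirms that the powered test is the change-score test.

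**Variance of the arm difference, in units of SD² × 4/N**
- Change score: 2(1 − r).
- ANCOVA on T1: 1 − r².
- Ratio: (1 + r)/2. Difference: (1 − r)².

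With unequal SDs s₁ and s₂, the change-score variance exceeds the ANCOVA variance by (s₁ − r·s₂)². This is never negative, so ANCOVA is never worse in large samples.

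| r | change | ANCOVA | variance cut | SE cut | source of r |
|---|---|---|---|---|---|
| .3 | 1.40 | 0.91 | 35% | 19.4% | assumed |
| .5 | 1.00 | 0.75 | 25% | 13.4% | assumed |
| .6 | 0.80 | 0.64 | 20% | 10.6% | assumed |
| **.7** | **0.60** | **0.51** | **15%** | **7.8%** | **Sample size, for fMRI** |
| .8 | 0.40 | 0.36 | 10% | 5.1% | assumed |

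**Cost of estimating the slope.** At N = 54 the ANCOVA variance is inflated by about 1 + 1/50, so 0.51 × 1.02 = 0.520. The cut is then 1 − 0.520/0.60 = 13%. A simulation of 20,000 trials with 27 patients per arm gives variances of 0.0446 (change) and 0.0388 (ANCOVA), also a 13% cut.

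**In patients.** At r = .7, ANCOVA with 60 × 0.85 = 51 patients matches change scores with 60.

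**Chance imbalance.** At r = .7, a 1 SD difference between arms at T1 shifts the expected difference in change by 1 − 0.7 = 0.3 SD. The SD of that imbalance at N = 54 is √(4/54) = 0.27, so a typical shift is 0.3 × 0.27 = 0.08 SD. This is the same gain seen another way, since 0.60 − 0.51 = 0.3² = 0.09. It should not be counted twice.

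**Power for the same 0.8 SD at N = 54 and r = .7.** Moving to ANCOVA raises power from 96.1% to 97.9% at α = .05, and from 45.6% to 55.8% at α = .00025.

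**The case against.** The strongest reply is that the article has not chosen differencing. AN(C)OVA is named one sentence before the difference scores, nothing says that those scores decide the comparison, and an unnamed covariate in a condensed article may well be fixed in a fuller plan. This stands. A reader might infer that the protocol uses change scores in place of baseline adjustment; the text does not support that. What remains is that the one test it powers is a change test and that its wording leaves open analyses which can give different answers.

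Second, the two-time-point equivalence fits the scans, while the difference-score sentence concerns behavioural data, and most scales are also taken at T3. This also stands. A three-time-point interaction is not one t-test. The variance formula applies to T2 or T3 singly, each set against T1.

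Third, the size. A reader might put the loss at up to a quarter of the precision. The 25% needs an assumed r of .5, because no correlation is given for the clinical scales. It is also a cut in variance, not in standard error.

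Fourth, patients are treated in groups of six, allocated in blocks of six per arm, so 60 patients form about 10 groups. The formulas assume independent patients, and large-sample reassurance is weaker with so few groups. ANCOVA removes imbalance in the measured T1 value only, not other differences between therapy groups.

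Finally, the intervention part is framed as exploratory, and change in brain signatures is a stated aim. That lowers the urgency. It does not favour the noisier estimator: at equal expected T1 values in randomised arms, both methods estimate the same arm difference.

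**Conclusion.** The point holds in limited form. For BAT versus MBT, the article powers a change-score test and plans difference scores beside AN(C)OVA without committing to the T1 value as covariate. Committing to it would cut the variance by about 15% at the documented r = .7, about 13% at 54 patients and about 8% in standard error. These figures assume equal SDs and independent patients, and the r is stated for fMRI only. For the clinical scales the cut lies between 35% and 10% over an assumed r of .3 to .8. Clustering by therapy group may change any of these figures.

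Two further inferences should be resisted. Adjustment does not rescue the stated 80% power: under the k = 200 correction at 54 patients it reaches 55.8%. The point also does not reach the four-group diagnostic comparison, which uses T1 data alone and is not randomised. This is a worthwhile, inexpensive improvement, not a flaw that invalidates the trial.

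**What to change.** In the data analysis plan, state that for BAT versus MBT:
- the T2 value of each region-of-interest measure is analysed by ANCOVA with arm and the patient's own T1 value as covariate (Table 1 has no T3 scan, so T2 only);
- the T2 and T3 values of each clinical scale, where measured, are analysed in the same way, each with its T1 value as covariate;
- difference scores are reported as description.

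The cost is one line of wording and one degree of freedom. T1 values of the neural measures and of the craving and depression scales are already scheduled. If AN(C)OVA was meant this way all along, the line makes it explicit. The change stands on its own and does not depend on any other change to the model.

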### Activation fMRI analysis

Preprocessing as well as statistical analyses of the experimental fMRI paradigms will be performed using SPM 12 (Wellcome Department of Cognitive Neurology, London, UK). In order to reduce systematic motion-related artifacts known to be especially prevalent in patient-control studies [55], we use the ART toolbox (http://www.nitrc.org/projects/artifact_detect) to detect outlier volumes. The ART software identifies outliers if the normalized z-score of the global mean intensity of a volume exceed a specified threshold and/or if extensive composite movement from a preceding image occurs. Preprocessing will be conducted with the standard procedure analysis including slice time correction, realignment, co-registration, normalizing, smoothing. Statistical analysis on the first (individual) level will be performed by modeling the different conditions using boxcar functions convoluted with the hemodynamic response function as explanatory variables within the context of the general linear model (GLM) on a voxel-by-voxel basis.

### Connectivity fMRI analysis

Task and resting state fMRI data will additionally be analyzed by connectivity approaches. To account for physiological and movement artifacts which strongly introduce artificial correlations into the data, heart beat and respiration will be monitored during scanning and physiological correction will be conducted with the software Aztec. Afterwards, images are preprocessed as described before by SPM 12. Task-dependent connectivity will be examined by functional connectivity and psychophysiological interaction analyses. Resting state data will be examined by conventional as well as dynamic functional connectivity analysis. Analyses in both task and rest will be conducted in a hypothesis-driven network-specific as well as more exploratory whole-brain manner [56]. The whole-brain results will be further analyzed by graph theoretical tools to elucidate relevant changes in functional network topology.

### Data management

The project data will be saved on the central server of the institute. The IT department professionally maintains the server; thereby a daily backup of all data is performed. Additionally, a network independent backup will be saved on local hard drive. Experimental data, as well as questionnaires will be saved in a pseudonymized form, separately from consent forms that contain the names of the participants. In addition, hard copy storage of reports, protocols, presentations or publication drafts will be realized. All data will be pseudonymized using unique study codes, which will be used to code and file all electronic information. The key linking this code to participant identity will be stored in a secured file, access to this key is available only to designated members of the research team. These researchers will have unrestricted access to all study data. As mentioned above, anonymized data will be made available for re- or meta-analysis after request.

## Discussion

Although there is significant knowledge of the environmental and neurobiological factors involved in depression and alcohol dependence, only a few studies have translated these empirical findings into a better understanding and treatment of comorbid patients. The planned project is set-up to transfer previous research about the reward circuit and default mode network underlying alcohol dependence and depression to achieve a better understanding of neural signatures characterizing their comorbidity. By means of diverse experimental paradigms allowing a comprehensive characterization of reward and default mode network activity and connectivity, we are planning to assess distinct and common mechanisms underlying comorbid alcohol and depressed patients. In addition, the neurobiological results will be used to test whether a brief psychotherapeutic intervention program is able to positively influence the identified pathomechanisms. By gaining a better understanding of diverse phenotypes and their underlying neurobiological signatures, it might be possible to improve clinical outcomes by offering specific types of psychotherapy. Furthermore, we should find support for our hypotheses that established behavioral and mindfulness based intervention programs specifically alter pathological neurobiological functions. By this, we will be able to identify neurobiological markers of therapy efficiency. The prediction of psychotherapeutic success based on neurobiological signatures will help to guide the selection of specific therapeutic options. Ultimately, by means of identifying and validating the use of objective, biological indicators associated with core mechanisms of mental disorders, advances in personalized medicine may be achieved.

One limitation of the study might concern the lack of a proper control group for the investigation of the treatment effects (for example waiting control group). However, this study was not designed to evaluate treatment effects per se but rather to investigate the neurobiological correlates of established psychotherapeutic interventions. With this, we are specifically interested if the targeted interventions positively alter the pathophysiology of comorbid patients and whether this is restricted to patients with a specific neurobiological signature. A second challenge affects the recruitment of comorbid depressed and alcohol dependent patients. Not only for the fMRI measurement, but also for the feasibility of the group therapy patients abstinence is a prerequisite. In order to motivate comorbid patients to participate in the group therapy and to stay abstinent, we want to guarantee a fast study enrolment, as well as ensure a short latency between study enrolment and begin of group therapy. For that reason, we decided for a group randomization of 6 participants per block. With this, we might risk recruitment-dependent biases. However, due to many different recruitment strategies and sources, we hope to reduce this potential bias to a minimum.

To reach the project results is one of the key issues and core challenges to contribute to a better neurobiological understanding and treatment of comorbid depression and alcohol dependence. The project will help to improve knowledge on pathophysiology, identify targets for treatment development, detect subgroups for treatment selection, and facilitate the use of neurobiology findings in the understanding of comorbid alcohol dependence and depression.

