## Methods

### Study design

In this randomized-controlled trial, comorbid alcohol dependent and depressed patients will be compared to depressed only, alcohol dependent only and healthy control participants. All participants are screened and after examination of inclusion and exclusion criteria admitted to the study. All participants will receive a baseline fMRI session (T1). Subsequently, only comorbid alcohol dependent and depressed patients will be randomized to either receiving group BAT or MBT training for 6 weeks. Afterwards comorbid patients will receive an outcome fMRI session (T2) and will be contacted after three months for a catamnestic exploration. For a flow chart of the study design please refer to Fig. 1.

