### Study procedure

Before participants will be finally included in the study, any open questions, risks and benefits will be discussed with a trained psychologist at the T1 assessment. On agreement of the participant, the informed consent form will be signed and a copy handed to the participant. Afterwards, participants will undergo a psychological interview assessing previously received therapy, current medication and for patients symptoms of depression or alcohol use disorder according to DSM-5. Before the fMRI measurement starts, all paradigms are explained to the participant. Also before and after the fMRI session, participants are asked to fill out questionnaires regarding their current mood and craving. Only comorbid alcohol dependent and depressed patients will be randomized to either receive BAT or MBT group training for 6 weeks. For comorbid patients, the fMRI procedure followed at T1 will be repeated at T2. Afterwards, comorbid patients will be contacted after three months for a catamnestic exploration. All participants will be compensated for their time with 15€ per scanning session plus the money won in the reward paradigm. To promote participant retention and complete follow-up we will contact the comorbid patients by phone during the follow-up period.

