### Additional information

The study protocol is in accordance with the Standard Protocol Items: Recommendations for Interventional Trials (SPIRIT) guidelines for reporting interventional trials. Ethical approval and consent has been obtained by the leading ethics committee of the Medical Faculty Mannheim/University of Heidelberg (reference number: 2015-606 N-MA). The study will be conducted in compliance with the guidelines for Good Clinical Practice and the Declaration of Helsinki. Participants will provide informed consent prior to enrolment in the study. The trial is registered in the German Clinical Trial Registration (DRKS00010249). Any changes to the protocol will be described in this trial registry.

The principal investigator (PK), independent from the sponsor and with no competing interests to report, is responsible for data monitoring. All adverse events are documented. Interim analyzes are not planned but cross-sectional comparisons for T1 data will be conducted after inclusion of all T1 participants and before data collections at T2 and FU are completed. The day-to-day management of the study (e.g. contact with the participants and the invitation to conduct online surveys) is carried out by advanced researchers. The publication of the results will be independent of the results of the study, even if the intervention proves to have no influence on brain activation and connectivity. Authorship eligibility will be decided according to the guidelines for safeguarding good scientific practice provided be the German Research Association [51]. A written summary of the results will also be made available to the participants after completion of the study. Data, statistical parameters and statistical code of the study will be made accessible to interested researchers after request. Due to data safety concerns, raw data cannot made openly accessible for the public.

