#### Resting state/mood induction paradigm

The so called mood induction paradigm has been successfully implemented in different studies [32]. Here, we will use a modified version of the paradigm in order to directly test intervention associated activation and connectivity patterns. The paradigm consists of five blocks, each of which lasts 4.5 min: a resting state block, a sad mood induction block, one alcohol cue-reactivity block, one mindfulness-based block and one behavioral activation block. The mindfulness-based block and the behavioral activation block are counterbalanced.

During the resting state phase, participants are told to keep their eyes open and background pink noise is presented. During the sad mood induction phase, key words to remind participants of personal negative life events and background sad music (excerpt from Albinoni/Giazotto, Adagio in g-minor) are presented. Participants are asked to concentrate on the negative life events and empathize with the situation. During the alcohol cue-reactivity phase, participants are presented images of either beer or wine (depending on the participants preference) while they receive corresponding audio induction statements instructing them to imagine alcohol-associated situations. In the mindfulness- based phase, again, participants are presented images of beer or wine while this time they listen to mindfulness-based audio instructions. Correspondingly, in the behavioral activation training phase, participants are played audio instructions associated with imagining activities while viewing alcohol-associated pictures. In each phase, 9 alcohol-associated cues are presented for 15 s, while simultaneously 9 audio statements are played. After each picture a fixation cross is presented for also 15 s. After each block, participants are instructed to rate their mood by means of the Positive and Negative Affect Schedule (PANAS), as well as their craving and self-control to abstain. For the T2 assessment, a different set of alcohol-associated pictures is presented.

As mentioned above, the mindfulness-based block and the behavioral activation block are counterbalanced. Thus, a second randomization list will ensure that at T1 the order of the experimental blocks will be equally distributed above all participants. Comorbid patients will receive the reverse order of their T1 assessment at the T2 fMRI scanning.

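### The plan still asks whether the programmes positively influence the pathomechanisms, but with two active arms and no rescanned comparison group it can show only a BAT–MBT difference; in the alcohol-picture blocks, picture set is also confounded with time

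*Protocol article*

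**What the plan says.** The Study design section states that "only comorbid alcohol dependent and depressed patients will be randomized to either receiving group BAT or MBT training for 6 weeks". Under Study procedure, "For comorbid patients, the fMRI procedure followed at T1 will be repeated at T2"; the alcohol-only, depression-only and healthy groups have a T1 scan and no other.

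The stated purpose is causal and directional. The Discussion announces that "the neurobiological results will be used to test whether a brief psychotherapeutic intervention program is able to positively influence the identified pathomechanisms", and the Abstract says much the same in its Background and Methods. The Discussion then admits: "One limitation of the study might concern the lack of a proper control group for the investigation of the treatment effects". It adds that "this study was not designed to evaluate treatment effects per se but rather to investigate the neurobiological correlates of established psychotherapeutic interventions". The very next sentence reads: "we are specifically interested if the targeted interventions positively alter the pathophysiology of comorbid patients".

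The Sample size section powers one intervention analysis, the BAT vs MBT group x time interaction (f = .2, correlation .7 between repeated measures, Bonferroni correction for 200 voxels). Behavioral data analyses also compares the two treatment groups. Primary outcome says that T1 identifies the neural signatures and T2 examines the influence of the interventions on them. Connectivity fMRI analysis plans both hypothesis-driven network analyses and exploratory whole-brain analyses. On timing, "cross-sectional comparisons for T1 data will be conducted after inclusion of all T1 participants and before data collections at T2 and FU are completed".

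For the mood-induction paradigm, "For the T2 assessment, a different set of alcohol-associated pictures is presented". The order of the mindfulness and behavioural-activation blocks is counterbalanced at T1 and reversed at T2. No counterbalancing is stated for the picture sets.

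**The concern.** The question asked and the comparison available do not match. If BAT and MBT work equally well, or if neither works, the randomised interaction is null in both cases. Only T1–T2 change in treated patients is left to support a statement that the programmes improve a pathomechanism, and nothing in the design supplies the change that would have occurred without them.

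A change over time is plausible without any treatment effect. Entry requires at least 5 days of abstinence before scanning, T2 follows six weeks of therapy, and patients with a severe relapse leave the protocol. Patients who reach T2 may therefore often have been abstinent for longer than at T1.

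Two narrower issues add to this. In the blocks that show alcohol pictures, every patient sees one set at T1 and another at T2, so a difference between the sets would look like a change over time. And if a T2 target is chosen because the comorbid group looked extreme on the T1 scan, and that same scan is the baseline, some movement back towards normal is expected by chance.

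At stake is whether a change that would have occurred anyway is reported as a corrected pathomechanism and then used to guide the choice of therapy, which the Aim and Discussion name as a goal.

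**Working it through.** **1. What each comparison can show.**

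| Comparison | Available? | What it answers |
|---|---|---|
| BAT vs MBT, change T1–T2 | Yes, randomised | Do the two programmes differ? |
| Treated vs untreated, change T1–T2 | No | Do the programmes change the mechanism? |
| Within-arm or pooled change T1–T2 | Yes, uncontrolled | Did the measure change, for whatever reason? |

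The directional question belongs to the second row. The plan has only the first and third.

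**2. The plan's own figure.** The only power figure for the intervention part is 80% for the interaction. With λ = f²·N·m/(1 − r) = 0.04 × 54 × 2 / 0.3 = 14.4, df = 1 and 52, power is 96% at .05 and 46% at .05/200 = .00025. The 80% is not reproduced at the stated correction. That is a separate matter and does not decide this point. No figure is given for T1–T2 change itself.

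**3. How a non-treatment drift would look in a pooled pre-post test.** Inputs: r = .7 and 60 patients less 10% drop-out = 54 (Sample size section); SD = 1; the drift is an assumption, shown as a range. SE = √(2(1 − r)/N) = √(0.6/54) = 0.105 SD. For a drift of 0.2 SD, the noncentrality is 0.2/0.105 = 1.90.

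| Assumed drift (SD) | Declared change at two-sided .05 | At .05/200 |
|---|---|---|
| 0.1 | 15% | 0.3% |
| 0.2 | 46% | 3% |
| 0.3 | 80% | 16% |
| 0.4 | 96% | 46% |

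**4. Selecting a target on the same T1 scan.** Assume 200 independent voxels, no true group difference, no true change, and the largest |Co − HC| difference taken as target (60 vs 30). Var(Co − HC) = 1/60 + 1/30 = 0.05, so the SD is 0.224. The part of the comorbid mean specific to the T1 occasion has variance (1 − .7)/60 = 0.005. The expected return at T2 is therefore 0.005/0.05 = 10% of the selected difference. The expected largest |z| among 200 is 2.97, so the shift is 0.10 × 0.224 × 2.97 = 0.066 SD.

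Simulation agrees: 0.06–0.07 SD at r = .7 and 0.10–0.11 SD at r = .5. At r = .7, change is declared in 9–10% of runs at two-sided .05, nearly all towards normal, and false normalisation occurs in about 0.1% of runs at .05/200. For one pre-fixed target the shift is at most about 0.02 SD at r = .7 (essentially nil at a true d of 1), and the error rate is about 5%. The BAT vs MBT interaction at the selected voxel stays at about 5% in every setting.

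**5. Picture set.** Alcohol pictures are described for the cue-reactivity, mindfulness and behavioural-activation blocks. The monetary, erotic and resting-state measures do not use them. Within the affected blocks, set and time coincide for every patient as written. No document gives a direction or size.

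**The case against.** The strongest reply is that the missing control group is disclosed, that the intervention part is described as exploratory, and that the only powered intervention analysis is the randomised contrast. No section names a within-arm or pooled pre-post test as confirmatory. All of this stands, so the point is not an unnoticed omission. It is a contradiction between a disclaimer and a question that the disclaimer rules out. Disclosure does not resolve it, because the directional question returns in the next sentence and also appears in the Abstract.

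A reader might go further and infer that the plan is biased towards apparent normalisation. The documents do not support that. The new pictures could push the measure either way and touch one paradigm; a fresh set also has a rationale, since it limits habituation. Carrying T1 peaks forward to T2 is not stated: the networks are named in advance from earlier literature, and the plan includes region-of-interest and hypothesis-driven network analyses. The exact list of regions may stand in the full protocol.

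A reader might also take the 9–10% or 46% as the error rates to expect from this plan. They are not. Both assume uncorrected .05 testing, while the Sample size section states Bonferroni correction over 200 voxels. The first also assumes peak selection among independent voxels, and the second an unsupported drift of 0.2 SD. At .05/200 they fall to about 0.1% and 3%.

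**Conclusion.** The concern holds in this form: the Abstract and Discussion keep a causal, directional question that the design cannot answer, because only treated patients are rescanned and both arms are active. This follows from the design and needs no numerical assumption. T1–T2 change cannot be separated from time, retest, longer abstinence or regression to the mean, and the size of these effects is unknown.

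Two smaller parts also hold. Picture set is confounded with time in the alcohol-picture blocks, in an unknown direction. Selecting a target from exploratory T1 results would add a modest shift towards normal, about 0.07 SD under r = .7 and peak selection of 200 independent voxels (spatial smoothing would reduce it), and close to nil for pre-fixed regions. The randomised BAT vs MBT contrast is not affected by the selection, and any drift or picture effect common to both arms cancels from it. The point should be acted on, but it does not undermine that contrast.

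**What to change.** - **Conclusion and wording.** Base the intervention conclusion on the randomised BAT vs MBT difference, label within-arm T1–T2 change descriptive, and reword the aims in the Abstract and Discussion so that they agree with the Discussion's own disclaimer. Cost: wording, and a more modest claim. Answering the directional question itself would need a concurrently rescanned untreated group, which is a different trial.
- **Picture sets.** Counterbalance the two alcohol picture sets across T1 and T2 within each diagnostic group, alongside the randomisation list that already governs block order. Cost: a change to the stimulus list and slightly more variance at T1; it can help only for patients not yet scanned. It removes the stimulus confounding, not the time effect.
- **Targets.** Where a T2 target comes from exploratory whole-brain T1 results and not from the a-priori networks, report its T1–T2 change as exploratory. Since T1 is analysed before T2 collection is complete, state before that analysis which targets are a priori. Cost: one sentence, or a reference to the list if the full protocol already holds it.
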